### Exclusion criteria

(1)Meet the classification and diagnostic criteria of The Diagnostic and Statistical Manual of Mental Disorders (DSM) for severe emotional and mental disorders;(2)Have a history of severe dependence on psychotropic drugs and sleep drugs;(3)Have a history of serious diseases of important organs (heart, liver, and kidney) or some sudden acute diseases;(4)Pregnant and lactating women;(5)Have more serious bad habits affecting sleep, such as smoking, drinking, and Internet addiction;(6)Recent major emotional trauma;(7)Any other circumstances that the researchers believe may make the patient unable to complete, comply with, or unsuitable for this study.

### Sample size

This study uses qualitative data group design sample size estimation formula:

$$n_{1}=n_{2}=\frac{\begin{array}{c} {}[z_{\alpha /2}\sqrt{P\,\left(1-P\right)\,\left(1+C\right)/C}\\ +z_{\beta }\sqrt{P_{1}\,\left(1-P_{1}\right)\,P_{2}\,\left(1-P_{2}\right)/C}]{}^{2} \end{array}}{{\left(P_{1}-P_{2}\right)}^{2}}$$

Among them, Zα/2 is the *Z*-value corresponding to the inspection level, Zβ is the *Z* value corresponding to the second type of error probability, *p* is the combined rate of two samples, and p1 and p2 are the two population rates, respectively, c is the ratio of the two sets of sample content, and the inspection level is specified as α = 0.05, test power 1-β = 0.9, c = 1, using a two-sided test, the clinical effective rate of insomnia treatment is calculated as an index. According to related research reports, p1 is 0.68, p2 is 0.92, and p is 0.80. Substituting the formula can get a total sample size of 114 cases (12). Considering possible withdrawal or loss to follow-up during research interventions, the sample size must be expanded to ensure the progress of the research. Therefore, the sample size is expanded by 10% on this basis, and the total sample size is for at least 126 cases.

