**Methods and analysis:**

This is a multicenter, single-blind, randomized controlled trial. A total of 126 eligible subjects who have passed the psychological evaluation and met inclusion criteria by completing a psychometric scale will be randomly divided into treatment group A (treat before sleep), treatment group B (treat after sleep) and control group C (waiting list group) in a ratio of 1:1:1. All the three groups will receive regular psychological counseling during the trial, and the treatment groups will practice 24-style Taijiquan and do meridian acupuncture at Baihui (DU20), Shenting (DU24), Yintang (EX-HN3), Shenmen (HT7) and Sanyinjiao (SP6). This RCT includes a 2-week baseline period, a 12-week intervention period, and a 12-week follow-up period. The main results will be measured by changes in the Pittsburgh sleep quality index (PSQI) and Hamilton anxiety scale (HAMA). The secondary results will be measured by the generalized anxiety scale (GAD-7) and insomnia severity index (ISI). The safety of the intervention will be evaluated at each assessment. The statistical analysis of data will be carried out by SPSSV.26.0 software.

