### Outcome measures

#### Primary outcome measurement

PSQI (19) assesses the sleep quality of the subjects, and HAMA (20) assesses the anxiety severity of the subjects and is jointly used to evaluate the effect of combined treatment. The evaluation time points are in the baseline period (week 2), the trial period (weeks 3, 6, 9, and 12), and the follow-up period (weeks 6 and 12).

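### The 90% power belongs to an insomnia effective rate that is not a listed outcome; no planning assumption is given for the primary PSQI and HAMA scores

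*Protocol article*

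**What the plan says.** The Sample size section uses a formula for comparing two proportions, and "the clinical effective rate of insomnia treatment is calculated as an index". Its inputs are "the inspection level is specified as α = 0.05", "test power 1-β = 0.9, c = 1, using a two-sided test" and "p1 is 0.68, p2 is 0.92, and p is 0.80". The result is reported as "Substituting the formula can get a total sample size of 114 cases", after which "the sample size is expanded by 10% on this basis, and the total sample size is for at least 126 cases".

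The outcomes are stated differently. The abstract says: "The main results will be measured by changes in the Pittsburgh sleep quality index (PSQI) and Hamilton anxiety scale (HAMA"). The Primary outcome measurement section names the same two scales: "PSQI (19) assesses the sleep quality of the subjects, and HAMA (20) assesses the anxiety severity". It sets no cut-off for response. The secondary outcomes are ISI and GAD-7. The Statistical analysis section assigns ANOVA and ANCOVA to measurement data and the CMH method to counts, and it names no binary efficacy outcome for CMH to analyse. Allocation is 1:1:1 to three arms.

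**The concern.** The only power statement in the article concerns a binary index that the trial does not list, compared by a test that is not the one for its primary outcomes. The index concerns insomnia, so HAMA, an anxiety scale, has no planning assumption of any kind. PSQI has no expected difference and no SD.

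At stake is the reading of the result. If PSQI or HAMA shows no difference, a reader will credit the trial with 90% power that was never calculated for either scale. This matters most for group A against group B. Those two active arms differ only in timing, choosing between them is a stated aim, and the true difference may well be smaller than that between treatment and waiting list.

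**Working it through.** **1. The plan's own figure.** Inputs from the Sample size section: p1 = 0.68, p2 = 0.92, pooled p = 0.80, two-sided alpha 0.05 (z = 1.960), power 0.90 (z = 1.282), c = 1. The standard formula is

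n per arm = [z_α/2 √(2p(1−p)) + z_β √(p1(1−p1) + p2(1−p2))]² / (p1−p2)²

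- First term: 1.960 × √(2 × 0.80 × 0.20) = 1.960 × √0.32 = 1.109
- Second term: 1.282 × √(0.2176 + 0.0736) = 1.282 × √0.2912 = 0.692
- n = (1.109 + 0.692)² / 0.24² = 56.27, rounded up to 57 per arm
- 2 × 57 = 114, and 114 × 1.10 = 125.4, rounded up to 126

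Both stated totals reproduce, so N rests wholly on the binary rate. (The formula as it appears in the text shows a product where a sum belongs under the second root. That may be a typesetting slip; 114 comes from the sum.)

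**2. What 114 means in three arms.** It is the total for two arms of 57. Spread over three arms it gives 114 / 3 = 38 per arm, and 126 / 3 = 42. Pairwise power for 0.68 against 0.92 is Φ{[0.24√n − 1.109] / √0.2912}:

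| n per arm | Power |
|---|---|
| 57 | 90% |
| 42 | 80% |
| 38 | 75% |

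**3. The primary outcomes.** With no difference or SD given, neither a required N nor a power can be computed. Only the detectable difference in SD units can be stated. For a pairwise two-sample t-test at 90% power:

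| Setting | 42 per arm | 38 per arm |
|---|---|---|
| Alpha 0.05, unadjusted | 0.716 SD | 0.753 SD |
| Alpha 0.05, ANCOVA, baseline correlation 0.5 (assumed): × √(1 − 0.5²) = × 0.866 | 0.62 SD | 0.65 SD |
| Alpha 0.025 (halved for two primary scales), unadjusted | 0.78 SD | 0.82 SD |

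At 80% power and alpha 0.05, unadjusted, the figures are 0.619 and 0.651 SD.

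**4. How far power depends on the missing input.** For the unadjusted t-test at alpha 0.05 with 42 per arm, power is about 27% at 0.3 SD, 62% at 0.5 SD and 95% at 0.8 SD. A figure of 90% therefore cannot be attached to PSQI or HAMA without naming a difference and an SD.

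**The case against.** Four arguments deserve an answer.

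*The rate may bear on PSQI.* If the effective rate dichotomises a roughly normal sleep score, 92% against 68% corresponds to 1.405 − 0.468 = 0.94 SD, and a t-test with 38 to 42 per arm would have about 98 to 99% power at that effect. This is fair as far as it goes, but the article does not define the rate, so the conversion is an assumption and does not establish power. For HAMA it offers nothing.

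*Categorical analysis is foreseen, and the full protocol may define the rate.* CMH is named for counts in general, without a binary efficacy outcome. The PSQI and HAMA cut-offs in the inclusion criteria are entry conditions, not definitions of response. A definition elsewhere would supply the missing threshold, but it would not turn this calculation into one for the stated primary outcomes.

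*An unadjusted t-test is not the only planned method.* This stands. ANCOVA is named, and at a baseline correlation of 0.5 it lowers the detectable difference by about 13%. The unadjusted figures should not be quoted alone.

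*Stronger readings go too far.* A reader might infer that the trial is underpowered for PSQI or HAMA. That depends on effects and SDs that the article does not give. A reader might also infer that the detectable effect is larger than the plan implies. The plan implies none for a continuous score, and on the conversion above 0.72 to 0.75 SD is smaller than 0.94 SD. Finally, a reader might suspect that an effective rate will be built once the data are seen. Nothing in the article supports that, and it provides for blind review and data lock.

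**Conclusion.** The point holds in a limited form: the sample size and its 90% power rest on an outcome the trial does not list, and the power for its two primary outcomes is unsupported. Underpowering is not shown.

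The size of the gap is best expressed as what the design can detect: at 90% power and two-sided 0.05, roughly 0.62 to 0.75 SD per pairwise comparison, depending on retention (38 to 42 per arm) and on whether baseline adjustment is used. It is about 0.78 to 0.82 SD unadjusted if alpha is halved for the two scales. These figures assume equal arms and normally distributed scores; the baseline correlation of 0.5 and the halved alpha are illustrations that do not come from the article. Even for the effective rate, 90% overstates the pairwise power, which is about 75 to 80% at the stated rates.

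**What to change.** In the Sample size section:

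- Stop presenting 90% as the power of the trial.
- Keep N = 126 and state, for PSQI and for HAMA, the pairwise difference detectable with 38 to 42 per arm. Give the assumed SD, the time point the sponsor selects, the alpha used, and whether the figure is unadjusted or from ANCOVA (with the assumed baseline correlation). The table under step 3 of the working supplies the values in SD units.
- Say whether that difference is one worth detecting. A detectable difference worked back from a fixed N does not by itself justify the N.

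If an effective rate is to be reported, list it as a secondary outcome, fix its threshold in advance, assign it to the CMH method already named, and attach no 90% power to it. State that 114 was a two-arm total and that pairwise power at 0.68 against 0.92 is about 75 to 80%.

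The cost is protocol wording and a sourced SD for each scale. No further participants are needed for this change.

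### The 114 cases are a two-group total (57 per group) spread over three arms, so each comparison with control has about 75–80% power, not the stated 90%

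*Protocol article*

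**What the plan says.** The Sample size section of the protocol article prints a formula for n1 = n2 with two rates and a group-size ratio c. Its inputs are:

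- significance level: "the inspection level is specified as α = 0.05";
- power, ratio and sidedness: "test power 1-β = 0.9, c = 1, using a two-sided test";
- rates: "p1 is 0.68, p2 is 0.92, and p is 0.80".

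The endpoint behind these rates is a clinical effective rate for insomnia treatment. The result is given as "Substituting the formula can get a total sample size of 114 cases (12"). After a 10% allowance for withdrawal and loss to follow-up, "the total sample size is for at least 126 cases".

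The design has three arms: before-sleep treatment (A), after-waking treatment (B) "and control group C (waiting list group) in a ratio of 1:1:1". The abstract, Study design, and Randomization and blinding sections all give this allocation.

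**The concern.** The formula returns the size of each of two groups. Nothing in the section extends it to a third arm, yet its two-group total is used as the total for a three-arm trial. Each arm then gets a third of the total, where the calculation assumed a half.

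If so, the stated 90% power does not apply to A versus C or to B versus C. A non-significant result in either would be read as stronger evidence of no effect than the design can supply, because the risk of missing the planned difference is about twice what the protocol states.

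The printed formula also looks wrong. Under the second square root it multiplies the two variance terms where the standard formula adds them, so a reader who follows the text cannot reach 114.

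**Working it through.** **Inputs (Sample size section).** Two-sided alpha 0.05 (z = 1.960), power 0.90 (z = 1.2816), c = 1, p1 = 0.68, p2 = 0.92, combined p = 0.80, difference 0.24.

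**1. Reproducing 114.** The standard two-proportion formula with c = 1 is

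n per group = [z(α/2)·√(2p(1−p)) + z(β)·√(p1(1−p1) + p2(1−p2))]² / (p1−p2)²

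- First term: 1.960 × √(2 × 0.80 × 0.20) = 1.960 × 0.5657 = 1.1087
- Second term: 1.2816 × √(0.2176 + 0.0736) = 1.2816 × 0.5396 = 0.6916
- n = (1.1087 + 0.6916)² / 0.0576 = 56.27, rounded up to **57 per group**
- Two groups: 2 × 57 = **114**, the protocol's figure exactly
- Three groups: 3 × 57 = **171**

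Could 114 instead be three groups of 38? At two-sided 0.05 and 90% power, the three-group total is 171 with the formula above, about 160 with unpooled variance or the arcsine method, and 195 with a continuity correction. None gives 114. Only 2 × 57 fits the stated inputs.

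**2. Numbers per arm.** 114 × 1.10 = 125.4, rounded up to 126. Then 126 / 3 = 42 randomised per arm, and 114 / 3 = 38 per arm after the planned loss.

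**3. Power per comparison with control.** Solving the same formula for power:

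Power = Φ{[0.24·√n − 1.1087] / 0.5396}

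| n per arm | Argument of Φ | Power | Exact chi-square power |
|---|---|---|---|
| 57 (required) | 1.303 | 90.4% | 92.1% |
| 42 (randomised) | 0.828 | 79.6% | 82.4% |
| 38 (after 10% loss) | 0.687 | 75.4% | 77.9% |

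Fisher's exact test would give 75.1% with 42 per arm and 69.2% with 38. These figures use the full 0.05 for each comparison. If alpha were split equally over the two comparisons with control (0.025 each, an assumption not in the document), the normal-approximation power would be 70.3% and 65.2%.

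**4. Pooling A and B against C.** This is not planned in the document but is worth checking. The same method with 2:1 group sizes and a combined rate of (0.68 + 2 × 0.92)/3 = 0.84 gives 88.3% for 76 versus 38 and 91.0% for 84 versus 42.

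**5. The formula as printed.** With the product under the second root, √(0.2176 × 0.0736) = 0.1266, and n = (1.1087 + 1.2816 × 0.1266)² / 0.0576 = 28.04, or 29 per group. That is 58 for two groups or 87 for three, so the printed formula does not produce 114.

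**The case against.** Four points can be made for the plan.

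**The contrast is not named.** The first aim is the effect of the combined therapy, and pooled A+B against C would have about 88–91% power with the same 126 participants. But no section plans that pooling, and n1 = n2 with c = 1 does not describe a 2:1 comparison. The aim of finding the better treatment time also requires A and B to be kept apart. This shows a possible remedy; it does not rescue the stated calculation.

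**The calculation concerns an effective rate, while the listed primary outcomes are PSQI and HAMA scores.** This stands as a limit on the finding. The document gives no mean difference or standard deviation, so power for the score comparisons cannot be derived, and 75–80% should not be read as power for them. The effective rate is nevertheless the only endpoint for which the protocol claims power, and that claim is wrong for the pairwise comparisons.

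**The main analysis is by intention to treat, so 42 per arm may be more relevant than 38.** This is reasonable if outcomes are available for all randomised participants. Power is then 79.6% (82.4% exact), still well below 90%.

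**The product in the formula is probably a misprint.** Agreed. The correct sum reproduces 114, so no number changes. It is a secondary erratum.

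**Conclusion.** The concern holds. The 114 is the total for two groups of 57, and the protocol divides it among three arms. On its own rates and two-sided alpha of 0.05, each active arm against control has 75.4% power with 38 per arm and 79.6% with 42 (77.9% and 82.4% by exact chi-square), not 90%. The risk of missing the planned effect is about 20–25% by the protocol's own type of formula, at least twice the stated 10%.

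This rests on three conditions: the endpoint is the effective rate used in the sample-size calculation, A and B are each compared separately with C, and there is no multiplicity adjustment. An adjustment would lower the power further. Power for A versus B cannot be computed, because the document states no effect size for it.

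**What to change.** Reword the Sample size section to:

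- give 57 as the requirement per group and 114 as the total for two groups;
- state that 126 participants in three arms means 42 randomised and about 38 evaluable per arm, with about 75–80% power for each of A versus C and B versus C on the effective rate;
- withdraw the 90% claim for those comparisons;
- replace the product under the second square root with a sum.

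This costs a few sentences and a less favourable power figure; it needs no extra participants.

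Two alternatives are design choices for the sponsor and are not needed to correct the error. Keeping 90% power for each comparison with control would take 171 evaluable participants, or 189 (171 × 1.10, rounded up) to 190 (171 / 0.9) enrolled with the 10% allowance. Naming pooled A+B versus C as the first efficacy contrast would give about 88–91% power with the existing 126 and address the first aim, but it would leave the separate comparisons at the lower figure.

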### Randomization and blinding

After the participants completed the baseline evaluation, they were randomly divided into treatment group A (treat before sleep), treatment group B (treat after sleep), and control group C (waiting list group) according to the proportion of 1:1:1. The random allocation sequence will be generated and hidden by the PLAN program using the statistical software SAS9.1. The random packet sequence is hidden by opaque and sealed envelopes, and the data statistician will not know the result of the allocation (15). This process ensures the full concealment of randomization and is not affected by the experimenter or subjects. Random assignments will be made after the first visit to participants who provide informed consent and meet the inclusion criteria. If the participant is eligible to be included in the study, the researcher will open the corresponding envelope in front of the participant. Envelopes will not be issued until all subjects have completed the baseline assessment. The subjects could not be blinded because of the unique nature of the intervention, but to ensure the scientific nature of the trial, the research team blinded trial evaluators and data, statistical analysts (16). To avoid misleading data analysts, researchers and subjects will be controlled to communicate with them to ensure that later data results are not affected by the subjective judgment.

### Interventions

The treatment groups will practice 24-style Taijiquan under the guidance of professional teachers. The training time is 15 min each time, once a day, for 12 weeks. The essentials of Taijiquan movements are based on the 24-style simplified Taijiquan compiled by the State Sports Commission (now the State Sports General Administration) in 1956 as the standard. The treatment groups will also carry out acupoint pressing training in the acupuncture and massage laboratory of Chengdu university of traditional Chinese medicine, mainly training Baihui (DU20), Shenting (DU24), Yintang (EX-HN3), Shenmen (HT7), and Sanyinjiao (SP6) acupoint positioning and thumb pressing and kneading techniques (17), while the pressing and kneading are required. Generally, pressing for about 1 min. It is appropriate that the patient feels obvious pain at the acupoints and can bear it. Participants will press the above five acupoints once or twice during the test time, and then change one acupoint for 1–2 min and then change one acupoint for a total of about 15 min. The subjects in the treatment group will receive compound treatment for 12 weeks, once a day for 30 min, including 15 min of 24-style Taijiquan and 15 min of acupoint pressing. To maintain the standard of the operation of the experiment, the subjects will practice for 3 days before the intervention, and after the movement is standardized, they will be trained every 2 weeks in Taiji Avenue and acupuncture and massage laboratory of Chengdu University of Traditional Chinese Medicine to avoid forgetting movements. The research team will assess the subjects on 24-style Taijiquan (a score of 60 or above is considered a pass) and if they fail they will be given additional training until they meet the assessment standard. See Table 1 for details of the scoring scale.

**TABLE 1 T1:** Taijiquan mastery rating scale.

Scoring items	Scoring criteria
Hand shapes, maneuvers, steps, footwork, legwork	2 points for each minor error; 3 points for each significant error; 5 points for each serious error; 6–10 points for multiple errors in one movement.
Smooth and precise force points consistent, rounded and coordinated movements	1–3 marks will be deducted for minor deviations from the requirements, 4–6 marks for significant deviations and 7–10 marks for serious deviations.
Natural, focused awareness appropriate speed and outstanding style	1–3 marks will be deducted for minor deviations from the requirements, 4–6 marks for significant deviations and 7–10 marks for serious deviations.
Forgetting the action	3–5 marks will be deducted for each instance of forgetfulness, depending on the degree.
Out of balance	1 point for each wobble; 2 points for each support; 3 points for successive supports.
Number of movements	3 marks will be deducted for each extra or missing movement.
Direction of movement	One point for each deviation of 45° or more from the prescribed direction.
Repeat the set	If the examination is interrupted due to forgetfulness or mistakes, the examination may be repealed once and 10 points deducted, and so on.
Unfinished sets	Those who do not complete the routine will not be graded and will be marked as failing.

A total of 100 points will be awarded, with a total score of less than 60 being unqualified.

Group A receives combined treatment 30 min before sleep. First, 24-style Taijiquan training will be performed for 15 min each time, once a day. Then do acupoint pressing at Baihui (DU20), Shenting (DU24), Yintang (EX-HN3), Shenmen (HT7), and Sanyinjiao (SP6), kneading 1∼2 times for 1∼2 min. And then replacing with the next acupoint, each acupoint will be kneaded 1∼2 back and forth, a total of 15 min of continuous pressing. After each treatment, study members should make strict records to ensure the full participation of subjects in the study (18). Group B does the therapy of Taijiquan combined with acupoint pressing 30 min after waking up, and the treatment procedures and methods are the same as those of Group A. Group C will not accept any intervention on Taijiquan or acupoint pressing, and maintain their normal lifestyle. After the study, subjects in this group can choose to participate in the treatment of 24-style Taijiquan training combined with acupoint massage.

### Follow-up

The purpose of follow-up is to evaluate the long-term effect of Taijiquan combined with acupoint pressing. After completing the treatment, a follow-up evaluation will be performed on the 15th, 18th, 21st, and 24th weeks. Participants will not accept any intervention but only complete the same scales as the trial period during the follow-up period. To encourage participants to comply with the rules, we will give special care to each participant and pay close attention to the changes in their sleep quality.

